# Stop or go? Preventive cognitive therapy with guided tapering of antidepressants during pregnancy: study protocol of a pragmatic multicentre non-inferiority randomized controlled trial

**DOI:** 10.1186/s12888-016-0752-6

**Published:** 2016-03-18

**Keywords:** Pregnancy, Antidepressants, Selective serotonin reuptake inhibitors, SSRI, Depression, Prevention, Relapse, Recurrence, Cognitive therapy, Perinatal outcome, Cost-effectiveness

## Abstract

**Background:**

Approximately 6.2 % of women in the USA and 3.7 % of women in the UK, use Selective Serotonin Reuptake Inhibitors (SSRIs) during their pregnancies because of depression and/or anxiety. In the Netherlands, this prevalence is around 2 %. Nonetheless, SSRI use during pregnancy is still controversial. On the one hand SSRIs may be toxic to the intrauterine developing child, while on the other hand relapse or recurrence of depression during pregnancy poses risks for both mother and child. Among patients and professionals there is an urgent need for evidence from randomized studies to make rational decisions regarding continuation or tapering of SSRIs during pregnancy. At present, no such studies exist.

**Methods/Design:**

‘Stop or Go’ is a pragmatic multicentre randomized non-inferiority trial among 200 pregnant women with a gestational age of less than 16 weeks who use SSRIs without clinically relevant depressive symptoms. Women allocated to the intervention group will receive preventive cognitive therapy with gradual, guided discontinuation of SSRIs under medical management (STOP). Women in the control group will continue the use of SSRIs (GO). Primary outcome will be the (cumulative) incidence of relapse or recurrence of maternal depressive disorder (as assessed by the Structured Clinical Interview for DSM disorders) during pregnancy and up to three months postpartum. Secondary outcomes will be child outcome (neonatal outcomes and psychomotor and behavioural outcomes up to 24 months postpartum), and health-care costs. Total study duration for participants will be therefore be 30 months. We specified a non-inferiority margin of 15 % difference in relapse risk.

**Discussion:**

This study is the first to investigate the effect of guided tapering of SSRIs with preventive cognitive therapy from early pregnancy onwards as compared to continuation of SSRIs during pregnancy. We will study the effects on both mother and child with a pragmatic approach. Additionally, the study examines cost effectiveness. If non-inferiority of preventive cognitive therapy with guided tapering of SSRIs compared to intended continuation of SSRIs is demonstrated for the primary outcome, this may be the preferential strategy during pregnancy.

**Trial registration:**

Netherlands Trial Register (NTR): NTR4694; registration date: 16-jul-2014

## Background

Depressive disorder and anxiety disorders are the primary indications for the use of Selective Serotonin Reuptake Inhibitors (SSRIs). Worldwide, the SSRI prescription rate during pregnancy ranges from 6.2 % in the USA [1], to 3.7 % in the UK [2]. The actual Dutch nationwide estimated use of SSRIs during pregnancy is about two percent [3, 4]; while in the Rotterdam area this number is even as high as five percent [5]. Nonetheless, SSRI use during pregnancy is still controversial. On the one hand SSRIs may be toxic to the intrauterine developing child, while on the other hand, relapse of depression and/or anxiety during pregnancy poses risks for both mother and child [6].

The preventive effect of SSRIs for relapse of depression during pregnancy seems equivocal. One naturalistic study showed a significant increased risk of relapse in pregnant women who discontinued their medication compared to continuing medication (68 % vs. 26 %), while another naturalistic study showed no clear difference relapse rates of depression (16 % in total) between pregnant women continuing or discontinuing antidepressants [7, 8].

Pregnancy-related complications both exist for women using SSRIs during pregnancy and women with untreated depression/anxiety during pregnancy, posing a dilemma for the treating physician who considers SSRI withdrawal. For example, studies found significantly increased risks for preeclampsia among women who use SSRIs and increased risks for pregnancy-induced hypertension in women with depression/anxiety during pregnancy compared to healthy controls [9, 10].

Whether or not SSRIs are of direct influence on the newborn, both short- and long-term, is another unresolved issue. For example, a recent meta-analysis showed an increased risk for cardiovascular malformations (RR = 1.36) and septal heart defects (RR = 1.40) with use of SSRIs [11]. These findings were however not supported by a recent Nordic cohort study, which – after a sibling controlled analysis – found no substantial increase in prevalence of overall cardiac birth defects for any SSRI (OR = 0.92) [12]. Another example of evidence of a potential direct toxic effect is the association of SSRI use with persistent pulmonary hypertension (PPHN) of the neonate. A large cohort study from the Scandinavian national health registers showed a twofold-increased risk of PPHN with exposure later than gestational week 20 (OR = 2.1) [13]. However, this risk appeared more modest (OR = 1.51) in a large cohort study from 46 US states [14].

Several other effects of SSRIs during pregnancy have been described, such as a higher risk of poor neonatal adaptation (OR = 5.07), respiratory distress (OR = 2.20), tremors (OR = 7.89), preterm delivery and small for gestational age, lower birth weight and lower Apgar scores at 1 and 5 min after birth [15, 16]. Long-term effects on children are less often investigated. One systematic review found an adverse effect on children’s motor development but not on emotional or behavioural development [17]. Two large studies reported on the association between maternal SSRI use and childhood autism spectrum disorders, but found conflicting results [18, 19].

On the other hand, leaving depression or anxiety disorders untreated may be hazardous to the unborn child as well. At present, it is well known that children of women who suffered from anxiety or depression during pregnancy have an increased risk of adverse perinatal health outcomes, and behavioural, emotional, cognitive, and motor problems in early childhood [20, 21]. It is also shown that the infant cortisol stress response is altered if the mother suffered from depression during pregnancy [22]. One meta-analysis showed an association of depression during pregnancy with preterm birth and low birth weight [23]. Another more recent meta-analysis showed that depression during pregnancy is associated with premature delivery, but did not find associations with birth weight, neonatal intensive care unit admissions, preeclampsia, gestational age or Apgar scores [24].

Overall, in clinical practice and literature, pregnant women express a strong preference for non-pharmacologic treatment of depression over antidepressant medication [25]. Hence, cognitive behavioural therapy (CBT) could be a good alternative for SSRI use during pregnancy. According to a recent meta-analysis there is strong evidence that CBT interventions are effective for preventing depressive relapse during the perinatal period [26]. A recent follow-up study showed that preventive cognitive therapy (PCT) has long-term effects in preventing depressive relapse in patients with recurrent depression for over 5.5-10 years after the sessions ended [27, 28]. This preventive psychological strategy therefore seems promising in preventing depressive relapse, presumably also during pregnancy. Moreover, a recent study in the UK among non-pregnant patients showed that tapering antidepressants with therapy was as effective as continuation of antidepressants (Hazard Ratio 0.89) [29]. Nevertheless, further investigation is necessary to assess effectiveness of tapering antidepressants with added PCT during the perinatal period.

In conclusion, pregnant women and their clinicians face a dilemma, which is widely experienced in current practice [30]. At present, there are no suitable data available to guide evidence based decisions on SSRI continuation or discontinuation during pregnancy [31]. Both the National Institute for Health and Clinical Excellence in the United Kingdom (NICE) guideline [32], and American Psychiatric Association (APA) [33] therefore recommend to discuss both possibilities with women. The recently developed Dutch multidisciplinary guideline advises to continue SSRI use during pregnancy, and furthermore advises a hospital delivery and neonatal observation based on the increased risk and the severity of the (rare) condition of PPHN and prevalence (25–30 %) of children with neonatal abstinence after maternal SSRI use [34]. Nonetheless, the need of randomized trials was stressed. Indeed, existing studies are observational and therefore their results do not fully allow causal inference nor definite conclusions for practice.

### Trial objectives

In this randomized controlled trial (RCT), the effect of preventive cognitive therapy (PCT) with guided tapering of SSRIs in early pregnancy will be compared to continuation of SSRIs during pregnancy. We will study effects on both mother and child with a pragmatic approach. The expectation is that tapering of SSRIs with added PCT does not increase the risk of clinically relevant maternal relapse or recurrence^1^ of depression or onset of anxiety disorders during pregnancy up to three months postpartum in excess of [absolute] 15 % compared to continuation of SSRIs. If so, discontinuation is deemed non-inferior with regard to relapse/recurrence risk. Furthermore, we expect that tapering of SSRIs is better than continuation of SSRIs with respect to child development. Finally, but not unimportantly, we hypothesize that discontinuation will decrease total costs per woman and child on a 3 months and projected long term base, assuming no relevant effects of discontinuation on the mother and no effects on the child are found.

## Methods/Design

### Design & setting

The Stop or Go study is a pragmatic multi-centre randomized controlled non-inferiority trial (RCT) in obstetric care. Women will be recruited during their first prenatal visit in midwifery practices (first echelon care) and hospitals (second and third echelons care), or through advertisement in (social) media. After inclusion, women will be randomly allocated into two groups: STOP or GO. Both groups will receive regular assessments throughout their pregnancy and up to 3 months post-partum. Permission will be asked to contact the Centre of Childhood (CJG) at 24 months after delivery for information on the development of the child. Total duration of the study for participants will therefore be 30 months. In Fig. 1 an overview of the study design and main procedures is shown.

**Fig. 1 Fig1:**
[figure not shown]
Study flow chart

### Participants

Women who are less than 16 weeks pregnant and use a SSRI primarily for depressive disorder, and are currently at least in remission or recovered [35], are invited to participate in the trial. Exclusion criteria are multiple pregnancy, as these women have a markedly increased obstetric risk, thereby threatening the homogeneity of the study population and thus potentially complicate the statistical analysis, and insufficient proficiency in Dutch or English, since our intervention is not yet available in other languages. Also, women will be excluded with severe medical conditions, such as oncology-related conditions or conditions that need urgent medical interventions, which involve treatment decisions overriding research participation. Exclusion criteria related to mental health are: current mania or hypomania or a history of bipolar illness, suicidality and serious self harm, any psychotic disorder (current and previous), current alcohol or drug misuse, predominant anxiety disorders and personality disorders that require psychotherapeutic treatment for more than 2 sessions a month.

### Assessment of eligibility

After informed consent is obtained, a pre-assessment interview will be conducted, with the Structured Clinical Interview for DSM-disorders (SCID) [36] and the Hamilton Depression Rating Scale (HDRS) [37] to assess major DSM-IV Axis I psychiatric diagnoses and actual remission status and depressive symptoms respectively. Before randomization, study researchers will contact the medical professional who prescribed the SSRI medication to inform the professional about the study and discuss exclusion criteria as described above for study participation.

### Randomisation

Two hundred women will be randomized in a 1:1 allocation ratio to either the intervention arm (STOP) or the care as usual arm (GO). Randomization will be done with a web based computer-generated randomization schedule (a validated TENALEA Clinical Trial Data Management System; http://www.formsvision.com/) using permuted blocks of random size with a maximum of 16 and stratified for the number of previous depressive episodes (dichotomized). Based on a recent review [35], the participants are divided into groups of participants with 3 or less previous depressive episodes, versus 4 or more. Allocation of participants is concealed for study researchers.

### Interventions

#### Tapering SSRI

Women assigned to discontinuation of SSRIs will be referred to a psychiatrist trained in guiding tapering of SSRIs during pregnancy. They will plan and carry out SSRI discontinuation using an expert-based discontinuation protocol [38]. The aim is to taper the use of SSRIs within four weeks, depending on patient preferences and on drug characteristics (e.g., half-life in the body). There are no restrictions on the use of medication like sleeping pills, paracetamol, and mild tranquillizers. All co-medication will be monitored during the study period.

### Preventive cognitive therapy

Trained psychologists will provide preventive cognitive therapy in the discontinuation arm. This psychological intervention has proven to be effective in relapse prevention [27, 39–42]. The current manual was evaluated in previous studies [27, 38, 41, 43].

The intervention will be applied through VSee (http://www.vsee.com), a HIPAA-compliant telehealth app. Several studies demonstrated that psychological intervention as applied by telephone support is effective and there is some evidence that it might be effective to decrease postpartum depressive symptomatology [44–47]. Although not tested during pregnancy, there are indications that antenatal telephone or online therapy is effective and convenient [48].

The preventive psychological intervention consists of a minimum of eight weekly VSee sessions. These sessions are led by professional psychologists trained in cognitive behavioural therapy and may occur at any time of the day. The focus of the sessions is on identifying and teaching the participants to challenge dysfunctional beliefs, enhance recall of positive feelings and cognitions and a personal prevention plan is developed in which it is specified how the participant can prevent a depressive episode in the future. For each session the participant will receive some assignments of approximately 10 min per day. Treatment adherence will be monitored.

### Care as usual

Women assigned to continuation of SSRIs (GO) obtain usual care. They will be instructed to consult their doctor as they regularly do, in line with the pragmatic nature of the study. All the care that is provided will be monitored.

### Outcome measures

#### Mother

Primary outcome of this trial is (cumulative) incidence of relapse or recurrence of a depressive episode (as defined by the SCID-I [36]) during pregnancy and up to 12 weeks postpartum. The SCID-I is assessed at baseline (T0) and 12 weeks postpartum (T6). If – based on assessment with the HDRS at fixed time-points – relapse/recurrence is suspected, the SCID-I will be performed intermittently.

For registration of severity of depressive symptoms, the HDRS will telephonically be assessed additionally, at baseline (T0), at 36 weeks of gestation (T3), and 12 weeks postpartum (T6), and also intermittently, if necessary [37]. When the HDRS at any stage turn out above cut-off scores, the participant will be called one week after initial measurement. The HDRS will be repeated to confirm or reject elevated scores. An adjusted telephonic version of the everyday problem checklist (EPCL) and pregnancy related life events will be assessed during each telephonic measurement (T0, T2, T3, T5 and T6).

Women will be asked to fill in questionnaires during five occasions: baseline (T1), 24 and 36 weeks of gestation (T2 and T3), and 4 and 12 weeks postpartum (T5 and T6). The questionnaires differ in composition at the five measurement moments, as shown in Table 1. During these occasions, participants are variably asked to report on anxiety symptoms (Dutch version of the State Trait Anxiety Inventory STAI), short and long version [49, 50]), depressive symptoms (the Dutch version of the Edinburgh Postnatal Depressions Scale; EPDS [51]), childhood trauma (Childhood Trauma Questionnaire; CTQ [52]), affect (the International Short-Form of the Positive and Negative Affect Schedule; I-PANAS-SF [53]), dysfunctional attitudes (Dysfunctional Attitude Scale; DAS [54]), medication beliefs (Beliefs about Medicines Questionnaire; BMQ [55]), medication adherence (Medication Adherence Rating Scale; MARS [56]) and Quality of Life (EQ-5D-5L [57]). Socioeconomic position, ethnicity, smoking behaviour, alcohol use, family history and information on previous pregnancies and family size will be assessed using the Mind2Care questionnaire [58], a screen-and-advice instrument to detect mental health problems among pregnant women.

**Table 1 Tab1:** Assessment per measurement moment

	Method	T0	T1	T2	T3	T4	T5	T6	T7
Clinical Diagnostic Interview (SCID-I)	Int	X		…	…	…	…	X	
Depressive symptoms (HDRS)	Int	X		…	X	…	…	X	
Peripartum depression (EPDS)	SR		X	X	X		X	X	
Anxiety (STAI)	SR		X	X	X		X	X	
Affect (I-PANAS-SF)	SR		X	X	X		X	X	
Attitudes (DAS)	SR		X	X	X				
Daily hassles	Int	X		X	X		X	X	
Life events	Int	X		X	X		X	X	
Sociodemographic & -economic factors (Mind2Care)	SR		X						
Substance use (Mind2Care)	SR		X	X	X		X	X	
Medication use	Int	X		X	X		X	X	
Medication adherence	SR		X						
Medication beliefs	SR		X						
Childhood trauma (CTQ)	SR			X					
Quality of Life (EQ-5D-5L)	SR		X	X	X		X	X	
Health care consumption (TIC-P)	SR		X		X		X	X	
Pregnancy related outcomes	CG					X			
Neural development (GM)	ME							X	
Child behaviour (CBCL)	SR								X
Cortisol (hair strands)	BM		X			X		X	
Buccal swab	BM		X					X	
Blood sample	BM							X	
Meconium (SSRI concentration)	BM					X			
Breast milk (SSRI concentration)	BM					X			

*Int* interview, *SR* self report, *CG* caregiver, *BM* biological materials, *T0* pre-assesment, *T1* baseline, *T2* 24 weeks of gestation, *T3* 36 weeks of gestation, *T4* delivery, *T5* 4 weeks postpartum, *T6* 12 weeks postpartum, *T7* 18 months postpartum

Health care cost data is registered using the TIC-P [59]. This instrument allows reliable recall over the past six months [60]. We will adapt scoring for ‘normal’ absenteeism and sickness leave for pregnant and recently delivered women. Care will be taken for secondary effects on child-care for other children (if present) in case of postpartum hospitalisation.

Using the Discontinuation Emergent Signs and Symptoms checklist (DESS) [61], the discontinuation group will be monitored by telephone weekly during tapering, to collect information about dosages and potential symptoms of withdrawal. Both groups will receive telephonic monitoring of medication use, including psychiatric co-medication, at 24 and 36 weeks of gestation (T2 and T3) and 4 and 12 weeks postpartum (T5 and T6).

Alongside the self-report measures, several sources of biological materials will be collected during the study. At baseline, immediately after delivery and 12 weeks postpartum (T1, T4 and T6) we will collect maternal hair strands to measure cortisol levels. Hair cortisol is a validated biomarker for long-term cortisol exposure and makes it possible to create a timeline of cortisol exposure during follow-up [62]. At baseline a maternal buccal swab will be collected in order to enable epigenetic and pharmacogenetic analysis. Maternal blood sampling will be performed 12 weeks postpartum (T6) to enable additional epigenetic and pharmacogenetic testing, but also for measurement of SSRI concentration and immunological factors.

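### Only one fixed depression screen (36 weeks) can trigger the diagnostic interview between baseline and 12 weeks postpartum; missed or unequally detected relapses can bias the non-inferiority comparison, in a direction that depends on detection by arm

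*Protocol article*

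**What the plan says.** All references are to the protocol article.

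- **Endpoint window** (Outcome measures, Mother): SCID-I relapse or recurrence "during pregnancy and up to 12 weeks postpartum".
- **Scheduled diagnostic interviews** (same section): "The SCID-I is assessed at baseline (T0) and 12 weeks postpartum (T6".
- **Interim SCID-I** (same section): done when relapse is suspected "based on assessment with the HDRS at fixed time-points".
- **HDRS schedule** (same section): "at baseline (T0), at 36 weeks of gestation (T3), and 12 weeks postpartum (T6), and also intermittently, if necessary". A score above cut-off leads to a repeat HDRS one week later.
- **Table 1**: the SCID-I has an X at T0 and T6 and dots at T2 to T5. The HDRS has an X at T0, T3 and T6 and dots at T2, T4 and T5. The legend does not explain the dots; I read them as the unscheduled route.
- **Contacts in both arms**: daily problems and life events "will be assessed during each telephonic measurement (T0, T2, T3, T5 and T6". The EPDS is completed at T1, T2, T3, T5 and T6 (Table 1). Neither the T2 and T5 calls nor the EPDS is linked to the HDRS or SCID-I.
- **Contacts in STOP only**: "the discontinuation group will be monitored by telephone weekly during tapering". STOP women also have at least eight weekly therapy sessions and a psychiatrist guiding the taper (Interventions). GO women have usual care.

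**The concern.** A cumulative incidence counts every episode in the window, including those that have resolved by the final visit. Women enter before 16 weeks, so more than 20 weeks (36 − 16) can pass before the only fixed interim HDRS, and this span holds the taper and the months after it. From T3 to T6 is about another 16 weeks (4 + 12, assuming delivery near 40 weeks). The Sample size section itself allows for SSRI treatment being restored after a relapse, so an episode that starts and remits inside one of these gaps is foreseeable.

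Two things are at stake. First, if a similar share of relapses is missed in both arms and STOP truly has more of them, the observed risk difference shrinks in proportion while the margin stays at 15 points, so non-inferiority becomes easier to declare wrongly. Second, the unscheduled route depends on someone noticing a need, and the opportunity to notice is much greater in STOP. Detection that differs by arm shifts the risk difference by an amount that cannot be separated afterwards from a treatment effect. Sparse assessment also blurs the onset times used in the Kaplan-Meier and Cox analyses.

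**Working it through.** **Inputs from the documents.** Margin 15 points; assumed relapse risk about 15%; one-sided alpha 0.025; power 80%; 178 women (Sample size); allocation 1:1 (Randomisation).

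**Assumptions, not in the documents.** Detection probabilities s_STOP and s_GO are varied over a range. True risks are set at the margin: 30% in STOP, 15% in GO.

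**Step 1: reproduce the plan's figure.** With 15% in both arms and unpooled variance,

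n per arm = 2 × 0.15 × 0.85 × (1.960 + 0.842)² / 0.15² = 88.95, rounded up to 89, so 178 in total. This matches.

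**Step 2: effect of missed relapses.** The observed risk in each arm is detection × true risk, so

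observed RD = 0.30 × s_STOP − 0.15 × s_GO.

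Non-inferiority is declared when the upper limit of the two-sided 95% Wald interval for STOP minus GO is below 0.15. Its probability was computed exactly from the two binomial distributions with 89 per arm. As a check, the normal approximation is

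Φ((0.15 − RD) / SE − 1.96), with SE = √[p_STOP(1 − p_STOP)/89 + p_GO(1 − p_GO)/89].

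Example with 0.8 in both arms: p_STOP = 0.24, p_GO = 0.12, RD = 0.12. SE = √[(0.1824 + 0.1056)/89] = 0.0569. Then Φ(0.03/0.0569 − 1.96) = Φ(−1.43) = 7.6%. The exact value is 8.0%.

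**Step 3: results.**

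| Detection STOP | Detection GO | Observed RD (points) | False non-inferiority, exact | Normal approx. |
|---|---|---|---|---|
| 1.0 | 1.0 | 15.0 | 2.6% | 2.5% |
| 0.9 | 0.9 | 13.5 | 4.6% | 4.4% |
| 0.8 | 0.8 | 12.0 | 8.0% | 7.6% |
| 0.7 | 0.7 | 10.5 | 13.8% | 13.0% |
| 0.6 | 0.6 | 9.0 | 22.8% | 21.8% |
| 0.7 | 0.8 | 9.0 | 19.9% | 19.1% |
| 0.9 | 0.8 | 15.0 | 2.7% | 2.5% |
| 0.9 | 0.7 | 16.5 | 1.5% | 1.3% |

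With 100 per arm, 0.8 in both arms gives 8.4% (exact).

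**Step 4: where the bias changes sign.** Setting 0.30 × s_STOP − 0.15 × s_GO = 0.15 gives s_STOP = 0.5 + 0.5 × s_GO. For s_GO = 0.8 the break-even is 0.9. Below it the bias is towards non-inferiority; above it, against.

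**Step 5: equal true risks.** At 15% in both arms, equal under-detection leaves the RD at zero and only raises power, from 80% to about 87% at detection 0.8 (normal approximation).

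**The case against.** The plan does provide for interim assessment. The dots in Table 1 stand at T2, T4 and T5 for both instruments without distinction by arm, the text allows the HDRS when needed, and a raised score at any stage leads to a repeat call. An exact trigger is operational detail that an article may leave to the full protocol. This stands in part: the unscheduled route will recover some relapses. It does not change the fixed schedule, which the article states and tabulates, and it leaves two existing contacts in both arms (the T2 and T5 calls and the EPDS) unused for the primary outcome.

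A reader might infer that the T6 SCID-I looks only at current state, so that every remitted relapse is lost. The article does not say that. A cumulative-incidence endpoint and a time-to-relapse analysis both fit an interview that looks back, and with a look-back much of the loss would be recovered, subject to recall. The article simply leaves this unstated.

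A reader might also infer that the design is biased towards non-inferiority. That is not supported either. The documented asymmetry in contact points to better detection in STOP, which can cancel or reverse the attenuation. Quicker remission in STOP after treatment is restored would work the other way. The net sign cannot be read from the article.

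Finally, the detection rates have no source in the article, and the table places the truth exactly at the margin. Under the planning assumption, taken as equal risks, equal under-detection causes no bias. This is correct, but the type I error of a non-inferiority test is defined at the margin, so that is where it should be examined.

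**Conclusion.** The point holds as a weakness in ascertainment with a conditional bias. T3 is the only fixed HDRS, and so the only scheduled trigger for an interim SCID-I, between T0 and T6; the unscheduled route has no stated criterion, and contact is much heavier in STOP.

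The size is hypothetical. With true risks of 30% and 15% and 89 per arm, equal detection of 0.9 to 0.7 moves false non-inferiority from 2.6% to between 4.6% and 13.8%. Better detection in STOP brings it back to 2.7% (0.9 against 0.8) or below nominal, at 1.5% (0.9 against 0.7). These figures show that the conclusion can be sensitive to detection; they do not estimate what this trial will miss. A look-back at T6 would reduce the problem. The point does not invalidate the design: it is a cheap improvement.

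**What to change.** 1. In both arms, either give the HDRS in the T2 and T5 calls that already take place, or let a prespecified EPDS score at T2, T3 and T5 (already collected) trigger the HDRS and SCID-I by the same rule.
2. State that the T6 SCID-I covers and dates every episode since T0, for all women.
3. State the criterion for unscheduled HDRS and SCID-I assessments, identical in both arms, and record what prompted each one.
4. Only once screening at T2 and T5 is in place, add a sensitivity analysis restricted to relapses found through the common scheduled assessments. On the present schedule that would mean essentially T3 and T6; it would discard confirmed relapses and worsen the attenuation.

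Cost: a few minutes in two existing calls, or a scoring rule on a questionnaire already collected, plus wording. The downside is slightly longer calls and some additional SCID-I interviews.

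### With no lower gestational limit at entry and no TIC-P at 24 weeks, women with baseline before about week 10 exceed the cost instrument's stated six-month recall (minor; economic evaluation only)

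*Protocol article*

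**What the plan says.** Under Outcome measures, Mother, the article names one cost instrument: "Health care cost data is registered using the TIC-P". It supports this choice with the statement "This instrument allows reliable recall over the past six months". Table 1 marks the TIC-P at T1, T3, T5 and T6. T2 is also a questionnaire occasion, at which the EQ-5D-5L among others is completed, but the TIC-P is not marked there.

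Entry timing comes from two places. Participants gives only a ceiling: "Women who are less than 16 weeks pregnant". Design & setting gives the main recruitment route: "Women will be recruited during their first prenatal visit in midwifery practices (first echelon care) and hospitals", with advertisement as another. Neither sets an earliest week.

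On the early weeks in STOP, Tapering SSRI says "The aim is to taper the use of SSRIs within four weeks", and Preventive cognitive therapy specifies at least eight weekly sessions. Neither section dates the start relative to T1. Trial objectives gives the economic hypothesis: "we hypothesize that discontinuation will decrease total costs per woman and child".

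**The concern.** T1 to T3 is the only TIC-P interval that can exceed the recall period on which the article relies, and it is the interval in which the intervention starts. If the T3 questionnaire asks about a fixed six months, the first weeks after an early baseline are not covered at all. If it asks about everything since T1, those weeks are reported from beyond the period for which reliability is claimed. The article does not say which applies.

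The timing matters because the arms may differ most in those weeks. STOP has referral to a psychiatrist, tapering and therapy, while GO has usual care. Under Economic evaluation, a finding of non-inferiority leads to a cost-minimization analysis, in which costs are the only quantity compared, and a cost-utility analysis follows in any case. That section also expects the upfront investment in therapy to be balanced by later savings, so early costs are part of the question being asked.

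**Working it through.** **Inputs.** Recall: six months (Outcome measures, Mother). T2 at 24 weeks, T3 at 36 weeks, T5 and T6 at 4 and 12 weeks postpartum (Table 1). Entry: below 16 weeks, no lower limit (Participants). Taper: aimed at four weeks (Tapering SSRI). The lag from T1 to the start of the taper is not given; 0 to 3 weeks is assumed here. The six-month figure comes from a cited source, so it can be converted but not reproduced.

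**Step 1, recall in weeks.** 6 × 365.25 / 12 / 7 = 26.1 weeks.

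**Step 2, break-even.** 36 − 26.1 = 9.9, so T1 before about week 10 exceeds recall.

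**Step 3, uncovered weeks and overlap with the taper.** Gap = 36 − week at T1. Uncovered = max(0, gap − 26.1). Uncovered taper = max(0, min(4, uncovered − lag)).

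| T1 at week | Gap to T3 (weeks) | Outside recall (weeks) | Taper weeks outside recall, lag 0 / 1 / 2 / 3 weeks |
|---|---|---|---|
| 6 | 30 | 3.9 | 3.9 / 2.9 / 1.9 / 0.9 |
| 7 | 29 | 2.9 | 2.9 / 1.9 / 0.9 / 0 |
| 8 | 28 | 1.9 | 1.9 / 0.9 / 0 / 0 |
| 9 | 27 | 0.9 | 0.9 / 0 / 0 / 0 |
| 10 | 26 | 0 | 0 / 0 / 0 / 0 |
| 14 | 22 | 0 | 0 / 0 / 0 / 0 |

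Nearly the whole four-week taper is uncovered only with T1 at about week 6 and no lag. With a lag of two weeks or more, T1 at week 8 or later leaves no taper week uncovered.

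**Step 4, the other intervals.** T3 to T5 is 40 + 4 − 36 = 8 weeks for delivery at 40 weeks and 42 + 4 − 36 = 10 weeks for delivery at 42 weeks (assumed delivery dates). T5 to T6 is 12 − 4 = 8 weeks. All are well inside six months.

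**Step 5, what the stated study duration says about entry.** Total participation is 30 months, of which 24 follow delivery, leaving 6 months in pregnancy. Taken literally with delivery at 40 weeks, entry is at 40 − 26.1 = 13.9 weeks, where the T1-to-T3 gap is about 22 weeks. If 30 is a rounded figure, it is less informative: entry at week 16 gives 24 weeks, or 5.5 months, before delivery and 29.5 months in total. The figure suggests later entry but does not exclude entry before week 10.

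**The case against.** The case against has four parts.

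- **Few women may be affected.** The 30-month duration points to entry near week 14, and consent and a pre-assessment interview come between recruitment and baseline. This stands as a limit on size: the share with T1 before week 10 is unknown and could be negligible. It does not remove the mismatch for those whom eligibility admits.
- **The intervention is recorded elsewhere.** STOP women are telephoned weekly during tapering about doses and withdrawal symptoms, therapy adherence is monitored, medication use is asked about at T2, T3, T5 and T6, and care in GO is monitored. This largely stands. The article does not say that these records feed the costing, and the weekly calls and the adherence monitoring, as described, do not cover sick leave or other care contacts. The exposure therefore narrows to those items.
- **A reader might infer that the uncovered weeks are the taper and first therapy weeks, and that costs are therefore biased towards the hypothesis of savings.** The document does not support this. It does not date the start of either component relative to T1, uncovered weeks are lost in both arms, and it gives no cost figures. A larger loss in STOP is possible but not shown.
- **A reader might also infer that the early period lies at the edge of recall for every woman.** It does not: with T1 at weeks 14 to 15 the gap is 22 to 21 weeks, some 4 to 5 weeks inside the limit.

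A full protocol may specify the recall wording and the sources of intervention costs. That would not change the schedule, which Table 1 fixes.

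**Conclusion.** The point holds in a limited form. The TIC-P schedule and the open lower end of eligibility together allow a T1-to-T3 interval longer than the recall period the article cites, for any woman with T1 before about week 10. The excess is about 1 week at week 9 and about 4 weeks at week 6. This rests on reading six months as 26.1 weeks and on T3 taking place at week 36.

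Whether the uncovered weeks contain taper or therapy depends on an unstated lag. What is mainly at risk is other care use and absenteeism shortly after baseline, possibly more in STOP. Only the secondary economic evaluation is touched; the primary relapse outcome is unaffected. Severity is minor.

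**What to change.** Mark the TIC-P at T2 (24 weeks) in Table 1, and word it there and at T3 to ask about the period since the previous questionnaire. The pregnancy intervals then become 24 minus the entry week, and 36 − 24 = 12 weeks. For entry at week 6 the first is 24 − 6 = 18 weeks, and even for entry at week 4 it is 20 weeks. Every interval is then within six months, whatever the distribution of entry weeks or the lag to the taper, and recall is shorter for all participants.

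The cost is one more questionnaire at an occasion when women already complete self-report forms, so slightly more burden and some added risk of incomplete forms. No new visit is needed.
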